#### PROMs assessment

Changes in patient-reported health-related quality of life (QoL)/PROMs will be assessed using the following validated questionnaires: Expanded Prostate Cancer Index Composite-26 (EPIC-26) (prostate cancer-related QoL and functional outcomes), European Organization for the Research and Treatment of Cancer Quality of Life Questionnaire (EORTC QLQ)-C30 (general QoL Score) and IPSS (urinary and sexual functional outcomes). The specific time points for these evaluations are:

Baseline assessment (prior to salvage treatment).1 month post-treatment completion.3 months post-treatment completion.6 months post-treatment completion.12 months post-treatment completion.24 months post-treatment completion.

The PROMs and quality-of-life assessments will not require a separate face-to-face meeting as these will be posted out to the participants. Follow-up after 2 years will be according to local policy.

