### Consent and withdrawal

All participants will give written informed consent before entering the study and before any assessments or interventions related to the study are undertaken. Consent will be taken by the direct care clinical oncologist or a member of the RO-PIP research team, for example, clinical research fellow or research nurse. Optional consent will be sought for taking extra blood and urine samples for the translational study component. Participants are free to withdraw at any time, or at the discretion of the chief or principal investigator. In the event of withdrawal, any data collected up until that point will be kept and potentially included in any analyses.

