### Eligibility criteria

The inclusion criteria are: (1) male individuals aged over 18 years; (2) histologically confirmed locally recurrent prostate cancer (following previous radiotherapy no less than 2 years ago); (3) no metastatic disease; (4) able and willing to provide an informed consent to participate; (5) WHO performance status 0–2; (6) reasonable urinary function (International Prostate Symptom Score (IPSS)<20 and Qmax>10 mL/s on flow tests); (7) greater than 10-year life expectancy.

The exclusion criteria are: (1) patients who are unfit for a general anaesthetic due to other comorbidities; (2) clinical or radiological evidence of metastatic prostate disease; (3) any patient with a medical or psychiatric condition that impairs their ability to give informed consent; (4) contraindication or intolerance of magnetic resonance scanning; (5) prior prostatectomy; (6) history of inflammatory bowel disease.

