### Assignment of interventions

Following confirmation of written consent and eligibility, participants will be randomised into the trial by the Leeds Clinical Trials Research Unit (CTRU). Patients will be randomised on a 1:1 basis to receive either HDR-BT or SBRT. Patients will be randomised using stratified permuted blocks, stratified by recruiting site and previous androgen deprivation therapy (ADT) therapy. Randomisation will be performed centrally using the CTRU 9–5 telephone randomisation system. Authorisation codes and personal identification numbers, provided by the CTRU, will be required to access the randomisation system.

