#### Stereotactic body radiotherapy

Patients will receive five fractions of 7.25 Gy per fraction, which will be delivered alternate days over no more than 2 weeks to provide a total dose of 36.25 Gy. Radiotherapy may be delivered using CyberKnife, linear accelerator or MR-linear accelerator. Implanted prostate markers and SpaceOAR may be used as per centre standard of care.

GTV will be delineated based on the intraprostatic lesion defined on the multiparametric MRI with or without additional diagnostic PET-CT information; a CTV will be delineated comprising either the whole prostate or for focal treatment the GTV with a 3 mm margin constrained to the prostate boundaries. The CTV will then be grown by 3–5 mm (dependent on departmental policy and image guidance technique) to generate a PTV. The rectum, bladder, bowel loops (where appropriate) and femoral heads will be contoured as organs at risk.

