### Baseline and follow-up evaluation

Table 1 shows the full schedule of events.

**Table 1 T1:** Reirradiation options for previously irradiated prostate cancer schedule of events

Item\Time point	Baseline	During RT	1-month FU	3-month FU	6-month FU	12-month FU	18-month FU	24-month FU
Informed consent	x							
Registration	x							
Testosterone	x							
Confirmation of eligibility	x							
Randomisation to BT or SBRT	x							
Pretreatment prostate biopsy sample requested and stored	x							
Collection of clinical history and outcome data	x							x
Radiotherapy (BT or SBRT) details	x	x						
PSA test	x			x	x	x	x	x
Functional prostate mpMRI	x		x			x		
PROM assessment (EPIC-26, EORTC QLQ-C30 and IPSS)	x		x	x	x	x		x
Research blood test/urine	x		x	x	x			
Clinician reported adverse events		x	x	x	x	x	x	x

BT, brachytherapy; EBRT, external beam radiotherapy; EPIC-26, Expanded Prostate Cancer Index Composite-26; FU, follow-up; IPSS, International Prostate Symptom Score; mpMRI, multiparametric MRI; PROM, patient-recorded outcome measure; PSA, prostate specific antigen; EORTC QLQ, European Organization for the Research and Treatment of Cancer Quality of Life Questionnaire; RT, radiotherapy.

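### The baseline PROM has to precede salvage treatment but not randomisation, so it may be completed with the allocation known, which can bias change from baseline

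*Protocol article*

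**What the plan says.** Under PROMs assessment, the first questionnaire time point is given as "Baseline assessment (prior to salvage treatment". The same section says of the questionnaires that "these will be posted out to the participants", so that no separate face-to-face meeting is needed.

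Assignment of interventions sets the conditions for randomisation: "Following confirmation of written consent and eligibility, participants will be randomised into the trial". Completed questionnaires are not among them. In Table 1 the rows "Randomisation to BT or SBRT" and "PROM assessment (EPIC-26, EORTC QLQ-C30 and IPSS" are both marked in the Baseline column, with nothing to order them.

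Consent and withdrawal requires consent "before any assessments or interventions related to the study are undertaken". This puts the questionnaires after consent; it does not put them before randomisation. Eligibility criteria asks for "reasonable urinary function (International Prostate Symptom Score (IPSS)<20", so one IPSS value must be known before allocation. The article does not say whether that value is the PROM baseline.

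The section on stereotactic body radiotherapy adds, for that arm only: "Implanted prostate markers and SpaceOAR may be used as per centre standard of care".

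**The concern.** A baseline should be measured before anything that differs between the arms. Here the timing rule is tied to the start of treatment, which comes after randomisation. The Reporting section asks for the time from randomisation to delivery of treatment to be monitored, so the plan itself expects an interval. In that interval a patient can learn whether he will have an implant or external beam treatment and, in the SBRT arm, may have markers or a spacer placed. Either could change how he answers questions on urinary, bowel, sexual and general wellbeing.

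Patient-reported toxicity and its effect on quality of life form the key secondary endpoint, and PROMs assessment says that changes will be assessed. The Sample size section uses the estimated toxicity rates in judging whether a larger trial is feasible, and the exploratory MRI and cytokine outcomes are related to PROMs. If, for example, symptoms after marker placement worsened the SBRT baseline, later worsening in that arm would look smaller than it was. A patient who leaves on learning his allocation may also have returned no baseline form. Questionnaire compliance, itself a feasibility endpoint, would then depend on the allocation.

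**Working it through.** The article gives no SD, effect size or power calculation for the PROMs, so there is no stated figure to reproduce. The check is first textual, then an illustration.

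**Does any section close the gap?**
- PROMs assessment: before salvage treatment; randomisation is not mentioned.
- Assignment of interventions: consent and eligibility come before randomisation; questionnaires are not mentioned.
- Table 1: same column, no order.
- Consent and withdrawal: assessments follow consent only.
- Eligibility criteria: an IPSS is needed before randomisation, but not EPIC-26 or QLQ-C30.

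None requires the baseline set before randomisation. The sequence consent, randomisation, allocation known, postal baseline, treatment satisfies every stated rule.

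**How large could the effect be?** The only input from the article is n = 30 per arm (Sample size). Assumptions:
- a share q of one arm completes the form after allocation or preparation, with q from 0.25 to 1.0;
- the scores of those patients shift by d, from 0.1 to 0.5 SD;
- the other arm is unaffected;
- the SD is the same at baseline and follow-up, and their correlation is r = 0.5.

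Shift in the between-arm difference in mean change = q × d.

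Standard error of that difference, in SD units = √(2(1 − r) × 2/n) = √(2 × 0.5 × 2/30) = √0.0667 = 0.258.

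| q | d = 0.1 | d = 0.3 | d = 0.5 |
|---|---|---|---|
| 0.25 | 0.025 SD (0.10 SE) | 0.075 SD (0.29 SE) | 0.125 SD (0.48 SE) |
| 0.50 | 0.05 SD (0.19 SE) | 0.15 SD (0.58 SE) | 0.25 SD (0.97 SE) |
| 1.00 | 0.10 SD (0.39 SE) | 0.30 SD (1.16 SE) | 0.50 SD (1.94 SE) |

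The range is 0.025 to 0.5 SD, or about 0.1 to 1.9 standard errors. The mean change within the affected arm moves by the same q × d, so the matter does not depend on a between-arm test. One baseline serves all five follow-up questionnaires (1, 3, 6, 12 and 24 months), so the same shift enters each. Adjusting for baseline with a slope of 0.5 would halve it (0.5 × q × d) but not remove it.

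With every baseline completed before randomisation, q = 0 and this shift is 0. It is also 0 under the present wording if nobody completes the form late, or if late completion does not change the answers.

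**The case against.** The strongest reply is that a condensed article need not spell out the order of steps in a baseline visit, and that the full protocol may do so. The consent-and-eligibility condition need not be a complete randomisation checklist. That would answer a point resting on silence alone. Here the article does state a timing rule, and the rule is tied to the wrong event.

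Several limits do stand:
- Analysis is descriptive, without hypothesis tests, and the article says the study is not powered to compare the arms. The key secondary endpoint is worded as incidence as well as impact on quality of life, so change from baseline is only part of it.
- Future work describes a comparison of reirradiation with ADT alone, so a difference between SBRT and HDR-BT is not the central planning input for that trial.
- Markers and spacer are optional, and their timing relative to the questionnaire is not given.
- That patients know their allocation is inferred from two visibly different treatments and the absence of any described masking; it is not stated.
- A baseline close to treatment has some merit. ADT is discretionary and may start at any time up to the first salvage treatment, so an earlier baseline can fold ADT effects into the change. The present wording does not secure either position, because a form completed at any time before treatment complies.

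Translational MRI assessment pairs the baseline scan with the questionnaires, which might seem to block a change. The pairing is by nominal time point, so both can stay in the baseline window.

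A reader might infer that every change score is biased, or that patients will have two conflicting baseline IPSS values. The article supports neither. Bias needs both late completion and altered answers, and nothing says that a second IPSS is taken.

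**Conclusion.** The point holds as a weakness in a stated timing rule. The plan permits a baseline PROM that is no longer independent of allocation, and a baseline collected late cannot be recovered in analysis. It can bias the descriptive changes from baseline in the key secondary endpoint and can make missing baselines depend on allocation.

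The size is unknown. The range of 0.025 to 0.5 SD rests wholly on the assumed share affected, the assumed shift and the assumption that only one arm is affected; its lower end is negligible. Expressing it in standard errors also rests on the assumed correlation of 0.5. The IPSS would be protected if the eligibility reading were used as the baseline, but the article does not say so. It would be wrong to extend the point to the primary endpoint: recruitment rates are not biased by when questionnaires are completed. The change is worth making because it is cheap and has to be in place before baselines are collected.

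**What to change.** In PROMs assessment and Table 1, define the baseline EPIC-26, QLQ-C30 and IPSS as completed after consent and before randomisation, and so before any marker or spacer placement. Give the forms out at the consent or eligibility visit; follow-up forms can still be posted. Have the trials unit confirm the completion date at the existing telephone randomisation call and record it. State that the eligibility IPSS may serve as the baseline IPSS. The baseline mpMRI stays in the baseline window.

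No extra visit, instrument or patients are needed. The costs are that randomisation may have to wait until the forms are completed, which matters a little in a trial whose primary endpoint is recruitment, and that the baseline may lie slightly further from the start of treatment.

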#### Translational MRI assessment

All patients will have three multiparametric MRIs (including standard anatomical sequences and functional sequences), which will be paired with PROMs assessments at the same time points (at baseline and then post-treatment at 1 month and 1 year). The purpose of this imaging component is fourfold:

To optimise a multiparametric MRI scanning protocol across three institutions incorporating intravoxel incoherent motion (IVIM), dynamic contrast-enhanced imaging and blood oxygenation level dependent sequences.To evaluate image quality and reproducibility of prostate functional imaging for detecting tissue perfusion and hypoxia.To investigate prostate and pelvic anatomical and functional imaging changes related to prostate reirradiation and how this relates to patient-reported toxicity side effects (determined by PROMs).To study the multiparametric MRI changes seen in the prostate in association with biopsy derived hypoxia-associated gene signature.

MRI scans done within the research study will be stored on the Leeds Teaching Hospitals Picture Archive and Communication System (PACS) server and on the local hospital PACS server where the images were obtained.

#### Translational biological assessment

The aim of this study component is to collect biological parameters that are prognostic and predictive markers of radiotherapy response and correlate this with imaging. From a biological stance the following sample collection will be relevant for assessing this:

Tissue collection (prostate biopsy including original diagnostic and local recurrence sample) to measure the presence of a hypoxia-associated gene signature.Urine collection to measure the inflammatory response via damage-associated molecular patterns.Blood sample collection (20–30 mL) to measures changes in cytokine response following reirradiation and other proteomics analyses.

The long-term storage arrangement for the research data arising from these biological samples will follow The University of Manchester Biobank (site of processing for biological samples) good practice for research guidance on clinical samples. Participants will have the option to consent to making their biological samples available for future research. The biological sample research data will be stored for 20 years once the study has ended.

### Baseline and follow-up evaluation

Table 1 shows the full schedule of events.

**Table 1 T1:** Reirradiation options for previously irradiated prostate cancer schedule of events

Item\Time point	Baseline	During RT	1-month FU	3-month FU	6-month FU	12-month FU	18-month FU	24-month FU
Informed consent	x							
Registration	x							
Testosterone	x							
Confirmation of eligibility	x							
Randomisation to BT or SBRT	x							
Pretreatment prostate biopsy sample requested and stored	x							
Collection of clinical history and outcome data	x							x
Radiotherapy (BT or SBRT) details	x	x						
PSA test	x			x	x	x	x	x
Functional prostate mpMRI	x		x			x		
PROM assessment (EPIC-26, EORTC QLQ-C30 and IPSS)	x		x	x	x	x		x
Research blood test/urine	x		x	x	x			
Clinician reported adverse events		x	x	x	x	x	x	x

BT, brachytherapy; EBRT, external beam radiotherapy; EPIC-26, Expanded Prostate Cancer Index Composite-26; FU, follow-up; IPSS, International Prostate Symptom Score; mpMRI, multiparametric MRI; PROM, patient-recorded outcome measure; PSA, prostate specific antigen; EORTC QLQ, European Organization for the Research and Treatment of Cancer Quality of Life Questionnaire; RT, radiotherapy.

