Prostate BT involves the placement of sealed radiation sources into the prostate and offers the ability to deliver highly conformal high-dose radiation with a steep dose gradient and rapid fall off in dose, which minimises radiation toxicity to surrounding organs at risk, specifically the rectum and bladder.^15^ Advances in image-guided-targeted BT may allow for more precise and focused treatments.^16–18^ BT can be delivered either via a permanent low-dose rate seed implant (LDR-BT), or via high-dose-rate BT (HDR-BT), which uses a high-activity radiation source (eg, iridium-192) that is temporarily introduced into applicators that are placed within the prostate, typically over 1–3 fractions. HDR-BT is less susceptible to issues related to prostate oedema and seed migration that might complicate dosimetry following LDR-BT. Current evidence suggests that HDR-BT affords lower toxicity, increased tolerability with similar oncological control compared with LDR-BT.^19^

Previously, salvage EBRT techniques have been associated with higher rates of severe late toxicities and also poor local control.^20^ Stereotactic body radiotherapy (SBRT), involving the delivery of a high dose of radiation to a highly conformal target volume with a steep dose gradient in a small number of fractions, may have benefits. Potential advantages include increased sparing of normal tissues than other types of EBRT and being less invasive compared with BT.^21^ BT is also highly specialised and only available in specialist centres.

A prospective trial is required to describe the toxicity profiles for these two most promising options, HDR-BT and SBRT, to allow clinicians and patients to make an informed decision on the most appropriate salvage treatment choice and help inform a larger study with an efficacy endpoint. Strategies to personalise salvage treatment through finding predictive genomic and imaging biomarkers are also required to optimise treatment outcomes.

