#### Toxicity assessment

Clinician reported treatment toxicity will be summarised at each time point as the proportion of patients experiencing each toxicity, summarised by maximum grade experienced as per Common Terminology Criteria for Adverse Events (CTCAE) V.5.0.

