#### Secondary outcomes

Incidence of patient-reported acute (0–3 months) and long-term toxicity (>3 months) and impact on QoL determined by EPIC-26 (prostate cancer related QoL and functional outcomes), EORTC QLQ-C30 (general QoL score) and IPSS (urinary and sexual functional outcomes) measurements (key secondary endpoint).Incidence of clinician-reported treatment toxicity as per CTCAE V.5.0.Other feasibility endpoints include screening log summaries, treatment and questionnaire compliance, withdrawal rate and reasons for non-recruitment.

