### Reporting

No formal interim analysis will take place; however, a study report will be produced for review by the independent data monitoring and ethics committee (DMEC) approximately midway through the study. The aim of the report is to evaluate and monitor the key study objectives (ie, recruitment rates, number of participants taking up their treatment allocation), as well as expected adverse events (AEs) and serious AEs and the delivery time of HDR-BT or SBRT post randomisation.

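### Table 1 schedules no clinician-reported adverse-event assessment between randomisation and the first fraction, so harms of optional marker or spacer insertion in the SBRT arm may be missed while HDR-BT implant harms are captured

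*Protocol article*

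**What the plan says.** The section Baseline and follow-up evaluation introduces its schedule with "Table 1 shows the full schedule of events". In that table, consent, eligibility and randomisation are all marked at Baseline. The row "Clinician reported adverse events" is blank at Baseline and marked at During RT and at 1, 3, 6, 12, 18 and 24 months.

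The section on stereotactic body radiotherapy states: "Implanted prostate markers and SpaceOAR may be used as per centre standard of care". The HDR brachytherapy section names neither item. For HDR-BT the Introduction describes a source "temporarily introduced into applicators that are placed within the prostate", so the invasive step is part of delivering the treatment.

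Under Toxicity assessment: "Clinician reported treatment toxicity will be summarised at each time point as the proportion of patients experiencing each toxicity", by maximum CTCAE grade. Secondary outcomes lists this clinician-reported item separately from the patient-reported one, "Incidence of patient-reported acute (0–3 months) and long-term toxicity (>3 months"), and labels only the patient-reported item as key.

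For the questionnaires, PROMs assessment fixes the first time point only as "Baseline assessment (prior to salvage treatment"), and the forms are posted to participants.

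**The concern.** The observation window for clinician-reported harm opens at a treatment event, not at allocation, and the two arms place their invasive step on different sides of that opening. Instrumentation of the prostate in the HDR-BT arm happens inside the window. Marker or spacer insertion in the SBRT arm, where a centre uses it, happens before the window opens. A complication of insertion that starts and settles before the first fraction has no scheduled assessment at which it would be recorded.

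The toxicity rates by arm are one of the study's products. The Introduction says that a prospective trial is needed to describe the toxicity profiles of the two options, and it lists lower invasiveness as a potential advantage of SBRT. Under-recording of SBRT procedural harm would bear on exactly that comparison. It would do so in one direction, and the analysis could not recover events that were never collected.

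**Working it through.** There is no figure in the protocol to reproduce: the article gives no power calculation, no expected toxicity rate and no expected use of markers or spacer. The check is therefore a comparison of the text, followed by an illustration of scale.

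**Timeline by arm**

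| Step | HDR-BT | SBRT |
|---|---|---|
| Randomisation | Baseline column; no adverse-event mark | Baseline column; no adverse-event mark |
| Between randomisation and first fraction | No scheduled assessment; no marker or spacer named | No scheduled assessment; optional marker or spacer insertion |
| Treatment | Applicator placement and irradiation; adverse events marked | Five fractions; adverse events marked |
| 1 to 24 months | Adverse events marked | Adverse events marked |

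Placing insertion in the second row is an inference. The article gives no date for it, but the items are named as part of SBRT and serve its delivery, so they would follow allocation and precede the first fraction. The interval is one the trial intends to measure: the mid-study report to the data monitoring and ethics committee covers "as well as expected adverse events (AEs) and serious AEs and the delivery time of HDR-BT or SBRT post randomisation". That sentence does not say when adverse-event capture starts.

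**Scale, for illustration only**

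Inputs: n = 30 per arm (Sample size section); u = share of SBRT patients who have an insertion (assumed 0 to 100%); h = share of those with a gradable harm (assumed 2 to 10%). It is further assumed that every such harm starts and resolves before During RT, and that these patients have no other event of the same kind that would count them anyway.

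- Expected patients missed = n × u × h
- Understatement of the SBRT rate = u × h
- Probability of missing at least one = 1 − (1 − u × h)^30

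| u | h | Expected missed | Understatement | P(at least one) |
|---|---|---|---|---|
| 0% | any | 0 | 0 points | 0 |
| 33% | 2% | 30 × 0.33 × 0.02 = 0.2 | 0.7 points | 0.18 |
| 67% | 5% | 30 × 0.67 × 0.05 = 1.0 | 3.4 points | 0.64 |
| 100% | 10% | 30 × 1.00 × 0.10 = 3.0 | 10 points | 0.96 |

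For comparison, the Wald 95% half-width at n = 30 is 1.96 × √(p(1 − p)/30): 10.7 points at p = 10%, 14.3 at 20% and 17.9 at 50%. The possible understatement is at most about the size of the sampling error, but it is systematic, and a confidence interval does not describe it.

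**Patient-reported baseline**

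Two orders are compatible with the wording. If the questionnaires are completed before insertion, any insertion effect still present at 1 month after treatment counts as change from baseline. If they are completed after insertion, the effect enters the baseline and the later change is reduced. In the HDR-BT arm a pre-treatment baseline necessarily precedes the implant. The article does not settle which order applies to SBRT.

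**The case against.** The strongest reply is that a schedule lists visits and does not define a reporting period. Nothing in the article excludes an event that began before the first fraction. One still present at During RT can be graded there, and the summary uses the maximum grade. The full protocol, which is not shown, may set a reporting period that starts earlier. This stands in part: a reader might infer that insertion harms are left out by design, and the documents do not say so. What remains is that the article presents this schedule as complete and starts the row at treatment, so harms that have resolved by then have no scheduled point of capture. If the full protocol starts earlier, the table should agree with it.

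A reader might also infer that the key secondary endpoint is affected in the same way. It is not: the key label belongs to the patient-reported item, while the gap in the table concerns the CTCAE item. Nor do the documents show that insertion symptoms are subtracted through the patient-reported baseline. An IPSS below 20 is an inclusion criterion and randomisation follows confirmation of eligibility, so an IPSS should exist before allocation. Table 1 also puts the questionnaires in the same column as randomisation. Still, the eligibility score need not be the posted baseline form, EPIC-26 and QLQ-C30 are not needed for eligibility, and the stated limit allows completion after insertion. This is an open timing, not a shown bias.

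Finally, the analysis is descriptive, the study is stated not to be powered for differences between arms, the primary endpoint is recruitment, and the larger trial described under Future work compares salvage reirradiation with ADT alone. All of this limits the consequence. It does not remove it, because the toxicity rates are reported by arm and are meant to be used in planning.

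**Conclusion.** The point holds in a limited form. Following Table 1 as written, procedural harm is observed in the HDR-BT arm but not reliably in the SBRT arm, so SBRT harms that resolve before radiotherapy may be missed in the clinician-reported CTCAE summary.

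The size cannot be derived from the documents. The range of 0 to 10 percentage points rests wholly on assumed uptake, an assumed harm rate and full resolution before radiotherapy. Zero is a genuine possibility because marker and spacer use is optional and left to centre practice. For the same reason the effect could differ between the three sites. No test, sample size or recruitment figure is affected. The unfixed patient-reported baseline is a lesser point of clarification. The change is worth making because it is cheap and must be made while data are being collected.

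**What to change.** In Table 1, start clinician-reported adverse events at randomisation in both arms. This needs no new visit: a query at the first radiotherapy visit covering the period since randomisation is enough. Under Toxicity assessment, state that events from procedures done for the allocated treatment, including marker or spacer insertion, count in that arm's CTCAE summary.

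As a secondary change, state under PROMs assessment that baseline EPIC-26, QLQ-C30 and IPSS are to be completed before any procedure done for the allocated treatment, in either arm.

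These are changes to data collection only and alter no treatment rule. The cost is one more mark in the table, two sentences and a short additional query. Reported SBRT toxicity may look slightly less favourable as a result.
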